## Abstract

**Background:**

With the gradual deepening of the aging of the population, the closely related problem of frailty in older people is becoming increasingly prominent. Frailty can increase the risk of bodily damage and adverse health outcomes such as falls, disabilities, hospitalizations, institutionalization, and death. Intermittent theta burst stimulation is a special stimulation mode of repetitive transcranial magnetic stimulation, which can enhance synaptic transmission by mimicking cortical theta rhythms. Some previous studies have suggested that intermittent theta burst stimulation is effective in improving balance function and motor function. However, few studies have explored the effects of intermittent theta burst stimulation to cerebellar vermis on balance function in frail older people.

**Objective:**

To introduce a randomized controlled trial protocol, which will be used to evaluate the efficacy of intermittent theta burst stimulation to cerebellar vermis on balance function in frail older people.

**Methods:**

This trial is a double-blind, two-arm randomized controlled trial. Frail older people with balance dysfunction will be recruited. All participants will be randomly assigned to experimental group who will receive intermittent theta burst stimulation to cerebellar vermis and control group who will receive false stimulation in a 1:1 ratio. All participants will also receive motor training once a day for 30–60 minutes each time, for a total of 20 sessions. The primary outcome will be balance function and the secondary outcomes will include frailty, walking ability, sensory organisation test, limits of stability, and rhythmic weight shift. All outcomes will be collected at baseline and in the week immediately post-intervention.

**Discussion:**

This study will be the first randomized controlled trial on the effects of iTBS to cerebellar vermis on balance function in frail older people. It is expected that this study, if proven effective in improving the balance function in frail older people, will provide evidence-based rehabilitation strategies for rehabilitation therapist.

**Trial status:**

Screening of participants will begin in September 2025.

## 1. Introduction

The aging of the world’s population is proceeding at an unprecedented rate, and by 2050, the population aged 60 and above is expected to increase to over 2 billion [1]. With the gradual deepening of the aging of the population, the closely related problem of frailty in older people is becoming increasingly prominent [2]. Frailty is a common condition in older people, which generally refers to a clinical syndrome characterized by a decline in functioning in multiple physiological systems [3]. The incidence of frailty among older people ranges from 4% to 59.1% in European countries [4], 6.1% to 9.0% in Japan [5], and 7.4% to 14.2% in China [6]. Frailty can increase the risk of bodily damage. Due to the loss of homeostasis, frailty may lead to a decrease in resistance to stressors and an increased risk of adverse health outcomes such as falls, disabilities, hospitalizations, institutionalization, and death [7]. These adverse consequences can seriously threaten the activities of daily living and quality of life of older people in their later years, bringing great medical and care burdens to family and society. Compared to healthy older people, the frail older people have sensory dysfunction, brain atrophy and brain dysfunction, cognitive decline, decreased muscle strength and decreased muscle mass, which may break the pathway of balance control and lead to balance dysfunction [8]. The balance dysfunction accompanied by frailty is an important factor that hinders healthy aging. It is of great significance for individuals, families and society to improve the balance function of the frail older population.

Frailty has the characteristics of systematicity, dynamism, and reversibility [9]. Targeted intervention programs may delay or even reverse the frailty of older people to a certain extent and prevent adverse health outcomes [10,11]. Balance control relies on a complete transmission pathway, that is sensory input-central integration-motor output, and is regulated through feedforward and feedback, which requires the participation and precise cooperation of various organ systems. The cerebellum plays a crucial role in balance control. The cerebellum is composed of the central vermis and bilateral enlarged cerebellar hemispheres. There are extensive fiber connections between the telencephalon, brainstem, and spinal cord, working together to regulate body balance, muscle tension and voluntary movements [12]. The cerebellar vermis plays an important role in maintaining balance and controlling movement. A previous study has found that the cerebellar vermis receives and integrates the sensations from the trunk and limbs, including various stimuli related to the formation of balance, vision and hearing, which are essential for maintaining balance, coordinating language expression, eye movement and trunk movement [13]. Balance stability correlates with cerebellar vermis volume [14]. In addition, the cerebellar vermis also participates in the anticipatory postural adjustment and compensatory postural adjustment of balance control during functional activities [15]. Patients with cerebellar vermis lesions mainly show balance dysfunction [16]. Moreover, an experiment showed that cerebellar vermis is a broad projection area of the cerebral motor cortex, and the cerebellum is closely connected to primary motor cortex, supplementary motor area, and dorsolateral prefrontal cortex through the cerebellar-thalamus-primary motor cortex circuit [17]. Although there is currently a lack of research directly using iTBS to stimulate cerebellar vermis to enhance balance function in frail older people, some studies have confirmed that iTBS to cerebellar vermis can effectively improve balance function in stroke patients and in patients with cerebellar-type multiple system atrophy [18,19]. Therefore, we can speculate that interventions targeting the cerebellar vermis may be effective in improving the balance function of frail older people.

Repetitive transcranial magnetic stimulation technology is a non-invasive brain stimulation that uses time-varying pulsed magnetic fields to act on the central nervous system, which induces current in the cortex, affects brain metabolism and nerve electrical activity, and thus regulates the structure and function of brain nerves [20]. Intermittent theta burst stimulation (iTBS) is a special stimulation mode of repetitive transcranial magnetic stimulation that can regulate neural plasticity, neurotransmitter and receptor sensitivity, cerebral blood flow, and promote the generation of brain-derived neurotrophic factor [21]. The application of iTBS in motor dysfunction after nerve injury has received widespread attention. Koch et al. [22] found that iTBS acting on the healthy cerebellar hemisphere of stroke patients can effectively improve their gait and balance function. Our previous study found that iTBS to cerebellum combined with motor training can effectively improve trunk control and balance function in patients with subacute and chronic stroke [23]. Furthermore, through functional near-infrared spectroscopy, it is suggested that iTBS to cerebellar vermis can improve healthy people’s cortical excitability of the supplementary motor area during balance tasks [24]. This points out that iTBS to cerebellar vermis can improve balance function by promoting cerebellar cortical plasticity. Therefore, the aim of this study is to introduce a randomized controlled trial protocol, which will be used to evaluate the efficacy of iTBS to cerebellar vermis on balance function in frail older people. The hypothesis is that iTBS to cerebellar vermis combined with motor training may be more effective in improving balance function of frail older people than false stimulation combined with motor training.

## 2. Methods

This study is a single-center, double-blind, two-arm randomized controlled trial with randomization at the participant level. This trial will be carried out based on the relevant guidelines and regulations of the Declaration of Helsinki. This trial was approved by the Ethics Committee of West China Hospital of Sichuan University (number: 2024−1075) and was registered on the Chinese Clinical Trial Registry (No: ChiCTR2400082918). Written informed consent will be obtained from all participants face to face. The schedule of enrolment, interventions, and assessments is shown in Fig 1. The screening of participants will begin in September 2025. The statement of the Consolidated Standard of Reporting Trials (CONSORT) will be used to guide the report of this study [25]. This protocol was guided by the Protocol of a Clinical Trial (SPIRIT) [26]. The balance function score will be the primary endpoint for examining whether iTBS to cerebellar vermis improve balance function in frail older people. All outcomes will be collected for the two groups at baseline (T0), at 10 days post-intervention (T1), and in the week immediately post-intervention (T2). Fig 2 shows the overview of the study design.

**Fig 1 pone.0339030.g001:**
[figure not shown]
The schedule of enrolment, interventions, and assessments.

**Fig 2 pone.0339030.g002:**
[figure not shown]
CONSORT flow diagram of this study.

### 2.1 Study setting and recruitment

This trial will be conducted at the department of rehabilitation medicine center of West China Hospital of Sichuan University in Chengdu, China. Researchers will recruit participants in the neurology ward. The recruitment program is planned to start in September 2025 and end in July 2027. Inclusion criteria of participants will be: aged 65 years and above; have balance dysfunction and the score of Berg Balance Scale < 56; have frailty and the score of Tilburg Frailty Indicator ≥ 5; no contraindications for iTBS, such as intracranial metal implants, cardiac pacemakers, and a history of seizures; no severe cognitive impairment and the score of Mini-Mental State Examination ≥ 17; stable vital signs and without serious heart, lung, circulation and metabolism diseases that are not suitable for motor training; voluntarily participate in this study and sign an informed consent form. The exclusion criteria will be: have other diseases except frailty that seriously affect the balance function, such as hemiplegia, paraplegia, Parkinson’s disease, lower limb fracture, spinal fracture, and amputation; participate in other clinical trials before. The dropping criteria will be: do not finish the training.

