### 2.2 Sample size

G Power software (version 3.1.9.2) will be used to calculate the sample size. The balance function measured by the Berg Balance Scale will be the primary outcome. According to a previous study on stroke patients [23], the estimated effect size is 0.380. Alpha is 0.05 (bilateral) and Beta is 0.10. Correlation between repeated measurements is 0.5 and non spherical correction is 1. The total sample size is calculated to be 40. Considering dropout and loss to follow-up, the total sample size is increased by 20%, and the final total sample size is 48.

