**Fig 3 pone.0339030.g003:**
[figure not shown]
The stimulation mode of iTBS. The iTBS mode will include 600 pulses, 3 pulses per bundle, with an intra bundle frequency of 50 Hz, stimulation of 0.04s, interval of 0.16s, inter bundle frequency of 5 Hz, continuous stimulation of 10 bundles, interval of 8s, and a total stimulation duration of 200s.

Participants in both groups will receive motor training for balance function. Professional physical therapists will design motor training programs for frail older people with balance dysfunction based on frequency, intensity, time, type, volume, and progression (FITT-VP) principles. The motor training will include muscle strength training, aerobic training, balance training, sensory training, flexibility training, and gait training. Each motor training will be conducted after the iTBS once a day. The training duration will be 30–60 minutes each time, for a total of 20 sessions.

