### 2.6 Statistical analysis plan

We will use IBM SPSS Statistics 23 to analyze the data. P‒P diagram will be used to test the normality of the distribution of measurement data. Mean and standard deviation will be used to describe normally distributed measurement data. The independent sample t-test and a paired-sample t-test will be used for comparisons. Ranking data and non normally distributed measurement data will be described by using the median and interquartile ranges. The Mann‒Whitney U test and Wilcoxon signed rank sum test will be used for comparisons. If the sample characteristics are different in baseline, subgroup analysis will be used. We will divide the participants into different subgroups based on certain characteristics, such as age, gender and educational level, and then analysis will be conducted within each subgroup. Counting data will be described by using number and percentage. Fisher’s exact test will be used for comparisons. Repeated measures analysis of variance (group * time) will be to examine the changes in all repeated measurement outcomes. If the baseline indicators are not comparable, an adjustment to the efficacy contrast of variables will be required. The intention-to-treat principle was used as the analytical strategy for outcome evaluation. *P* < 0.05 indicates statistical significance. All tests are 2-sided.

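### The rule that drops participants who do not finish training conflicts with the stated intention-to-treat analysis; if they are not followed, the result becomes a completers-only comparison

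*Protocol article*

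**What the plan says.** Four statements in the protocol article bear on this point.

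- Section 2.1, straight after the eligibility criteria: "The dropping criteria will be: do not finish the training".
- Section 2.4, on what has to be finished: "The training duration will be 30–60 minutes each time, for a total of 20 sessions". Both arms receive this training, each session following the real or sham stimulation.
- Section 2.2, on the sample size: "The total sample size is calculated to be 40", and then "Considering dropout and loss to follow-up, the total sample size is increased by 20%, and the final total sample size is 48".
- Section 2.6, on the analysis: "The intention-to-treat principle was used as the analytical strategy for outcome evaluation", with the model given as "Repeated measures analysis of variance (group * time) will be to examine the changes in all repeated measurement outcomes" and the software as SPSS 23.

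The article does not say whether a dropped participant is still assessed at T1 and T2, or belongs to the analysed set. It names no completers or per-protocol set.

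**The concern.** Intention to treat keeps every randomised participant in the arm assigned, whatever the adherence. A criterion that drops people for incomplete adherence does the opposite. These are two stated rules that pull in different directions, so this is more than a detail left to a fuller document.

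What is at stake is the population behind the primary Berg Balance Scale result. If non-finishers disappear, the groups compared are no longer those formed by randomisation. The participants are frail and the programme is long, so stopping may well be related to how balance is changing. The article does not define what counts as finishing (all 20 sessions, or most), and section 2.3 says that the researchers know the allocation. Who is classed as dropped could therefore be influenced by staff who know the arm. As the text stands, either population could be defended after the data are seen, and assessments not made at T1 and T2 cannot be recovered.

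**Working it through.** **1. The sample-size step.** Inputs from section 2.2: 40 needed, raised by 20%. 40 × 1.20 = 48, which reproduces the stated total. The allowance covers 48 − 40 = 8 losses, or 8/48 = 16.7%. A loss of 20% of those randomised would leave 48 × 0.80 = 38.4, about 38. The 40 is taken as given here; whether it follows from its own inputs is a separate question that does not affect this point.

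The allowance names dropout separately from loss to follow-up and subtracts both from the number needed. If people who stopped training were still assessed and analysed, stopping alone would cost no analysable participants. This suggests, but does not prove, that dropped participants leave the analysis.

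**2. What the named model does.** Repeated measures ANOVA in SPSS, run in the standard way, uses only cases with every visit present. A participant missing T1 or T2 is removed, baseline included. So if non-finishers are not assessed and no missing-data method is added, the analysed set is the completers.

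**3. When completers differ from all randomised.** Let p be the proportion of an arm that stops, and g the mean change in finishers minus the mean change in non-finishers, in SD units. The full-arm mean change is (finishers' mean) − p × g, so restricting to finishers raises the arm's mean by p × g. The between-arm bias is

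bias = p_A × g_A − p_C × g_C.

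- Equal p and equal g: bias 0.
- Assumed p = 0.20 and 0.05, g = 1 SD in both arms: 0.20 − 0.05 = 0.15 SD. With g = 0.5 SD: 0.075 SD.
- If non-finishers are lower by the same amount c at T0, T1 and T2, every visit mean in that arm rises by p × c. The change from baseline shifts by p × c − p × c = 0, so the group-by-time test is not biased. The gap has to be in change.

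**4. Simulation with assumed stopping patterns.** 24 per arm (48/2), no true effect, normal outcome with SD 1 (read as change in balance), 8,000 runs per row, two-sample t-test on completers. Participants with the lowest values of a latent variable stop; r is its correlation with the outcome.

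| Stopping, arm A / arm C | r, A / C | Mean bias (SD) | Type I error |
|---|---|---|---|
| 1/6, 1/6 | 0, 0 | −0.005 | 5.0% |
| 1/6, 1/6 | 0.5, 0.5 | 0.004 | 5.0% |
| 1/6, 1/6 | 0.5, 0 | 0.147 | 7.4% |
| 25%, 8.3% | 0.5, 0.5 | 0.129 | 7.0% |

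Check by formula: each arm's shift is r × φ(z_p)/(1 − p).

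- Row 3: 0.5 × 0.2499/0.8333 = 0.150.
- Row 4: 0.5 × 0.3178/0.75 − 0.5 × 0.1529/0.917 = 0.212 − 0.083 = 0.129.

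The bias favours the arm in which stopping removes more of the poor responders, so it can run either way.

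**5. A change in what is estimated.** If a proportion p of the iTBS arm stops and gains nothing, while finishers gain δ and stopping is otherwise unrelated to outcome, the effect as randomised is (1 − p) × δ. The completers' effect is larger by the factor 1/(1 − p): 1/0.80 = 1.25 at p = 0.20, and 1.20 at p = 1/6.

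**The case against.** The strongest reply is that the criterion is a single sentence in the recruitment section and may only define who is counted as a dropout. The one statement about the analysis population is intention to treat. Raising the sample size for dropout is also ordinary under intention to treat. A reader might infer that the plan prescribes a completers-only analysis, or that intention to treat cannot be delivered. The article supports neither: it does not say that dropped participants go unassessed or are excluded, and a missing-data method may sit in an analysis plan that is not shown. This part of the objection stands, and the completers-only consequence is conditional.

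A reader might also infer that intolerance of real stimulation will drive unequal stopping. The support is thin. The criterion concerns the training, which both arms receive, and section 2.4 answers intolerance by lowering the intensity. The article gives no stopping rates by arm. Nor is it sound to express 0.15 SD as a share of the planned effect: that requires reading "the estimated effect size is 0.380" as Cohen's f, and the article does not state the metric.

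Finally, a mixed model is not needed to remove the contradiction, which a sentence on follow-up and analysis would do. It is recommended because it uses the scores of participants with a missing visit.

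What remains is that the two rules conflict, nothing shown reconciles them, and both the dropout allowance and the default behaviour of the named model lean towards leaving non-finishers out.

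**Conclusion.** The conflict between the dropping criterion in section 2.1 and the intention-to-treat statement in section 2.6 is real and must be reconciled. If non-finishers are no longer assessed or are left out, the primary analysis becomes a comparison of completers. It is then biased when the link between stopping and change in balance, or the rate of such stopping, differs between the arms. The size is unknown. The 0.13 to 0.15 SD bias and the roughly 7% type I error illustrate assumed patterns and are not predictions; with stopping alike in both arms the bias is nil. The figure of 1.25 likewise assumes that 20% of the iTBS arm stops and gains nothing. The point is worth settling before recruitment because it fixes the population for the primary result and missed assessments cannot be made up later.

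**What to change.** Replace the dropping criterion with a statement that participants who do not finish the training remain in the study, are assessed at T1 and T2 unless they withdraw consent, and are analysed in the arm to which they were randomised. Record the number of sessions completed and the reason for stopping, by arm. This concerns follow-up and analysis only; it sets no rule on when anyone should stop training.

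Analyse the Berg Balance Scale with a linear mixed model for repeated measures (SPSS MIXED) with group, time and their interaction, using all available scores. Unlike default repeated measures ANOVA, it keeps participants with a missing visit. It still assumes that missingness depends only on observed data, so assessing those who stop remains the main protection. Report completers as a sensitivity analysis only.

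The cost is revised wording, a different procedure in software already named, and a few assessments, at visits already planned, of participants who stopped training. The expected effect will be somewhat smaller, because those who stop are counted.

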### 2.2 Sample size

G Power software (version 3.1.9.2) will be used to calculate the sample size. The balance function measured by the Berg Balance Scale will be the primary outcome. According to a previous study on stroke patients [23], the estimated effect size is 0.380. Alpha is 0.05 (bilateral) and Beta is 0.10. Correlation between repeated measurements is 0.5 and non spherical correction is 1. The total sample size is calculated to be 40. Considering dropout and loss to follow-up, the total sample size is increased by 20%, and the final total sample size is 48.

### 2.3 Randomization, allocation concealment and blinding

A 1:1 random number sequence will be generated based on a computer. After assessment at baseline, a research assistant will randomly assign eligible participants to one of two groups at a 1:1 ratio after the initial evaluation. The research assistant will place the randomized grouping schemes into some sequentially encoded, sealed, and opaque envelopes. All envelopes will be neatly stored in the locked filing cabinet of the research center in order of their entry numbers. The keys will be kept by the department secretary, who will not participate in any intervention. After evaluating the eligibility of participants and obtaining informed consent, the researchers will request the department secretary to open the envelopes in the order of enrollment to determine participants’ group. The researchers can not be blinded to the assigned interventions. Participants will be blinded to the allocation. Participants will only know that they will receive intervention when entering the group, but they will not know whether it is a real stimulus or a fake stimulus. The two intervention processes will be completely identical in operation. The data collector and statisticians will be blinded to the allocation. The data collector will only record the participant’s enrollment number during the evaluation and will not access any information related to the group. During the data entry and statistical analysis phase, the statisticians will only receive de-identified data labeled with group numbers.

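### Baseline Berg is balanced neither at allocation nor by a fixed adjustment; the primary model should always include it as a covariate, with Berg-stratified allocation as an optional extra

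*Protocol article*

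**What the plan says.** **Allocation (protocol article, 2.3).** The method is given as "A 1:1 random number sequence will be generated based on a computer". The assignments go into one numbered series of sealed envelopes, which the department secretary opens in the order in which participants enrol. No stratum or other balancing factor is named. Blocks are not mentioned, either as used or as not used.

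**Timing (2.3).** "After assessment at baseline, a research assistant will randomly assign eligible participants to one of two groups". The Berg score is therefore known when the envelope is opened.

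**Population and size (2.1, 2.2).** Participants must "have balance dysfunction and the score of Berg Balance Scale < 56", on a scale of 0 to 56. On numbers: "The total sample size is calculated to be 40", and after the dropout allowance "the final total sample size is 48".

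**Analysis (2.6).** Changes in all repeated outcomes are examined by repeated measures ANOVA with group, time and their interaction. For imbalance the section says: "If the sample characteristics are different in baseline, subgroup analysis will be used". A further sentence calls for adjusting the treatment comparison when the arms prove non-comparable at the start. It gives no criterion for that and names no covariate.

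**The concern.** Baseline Berg can be expected to predict later Berg: the sample size section itself assumes a correlation of 0.5 between repeated measurements. In a trial of 48 people it is worth controlling such a variable, either when participants are allocated or in the model. The plan fixes neither.

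Two things are at stake. The first is precision: an analysis of change removes baseline less efficiently than covariate adjustment does. The second is credibility: if the arms differ visibly at the start, the plan offers two alternative responses, chosen after the baseline data are seen and without a stated trigger. One of them, subgrouping within 48 people, leaves very small cells and does not correct the overall comparison.

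**Working it through.** **Inputs.** N = 48, effect size 0.380 and correlation 0.5 come from section 2.2. Assumptions: 0.380 is Cohen's f (the type is not named), so d = 2 × 0.380 = 0.76 SD; Berg scores are roughly normal; all 48 are analysed, 24 per arm; and, for the power figures, there is one post-baseline measurement. The documents give no baseline Berg SD, so results are in SD units.

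**The plan's own figure.** 40 × 1.2 = 48 reproduces. How the 40 was obtained is a separate matter and does not affect this point.

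**Step 1: chance of a baseline gap.** The SD of the difference in baseline means is √(2/24) = 0.289 SD.

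| Gap exceeding | z = gap / 0.289 | Probability, either direction |
|---|---|---|
| 0.3 SD | 1.04 | 30% |
| 0.4 SD | 1.39 | 17% |
| 0.5 SD | 1.73 | 8% |

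Simulation of simple allocation of 48 gave 31% above 0.3 SD and 9% above 0.5 SD. Blocks of 4 without stratification gave 30% and 9%. Blocking alone therefore does not change the Berg gap, and the result does not depend on whether blocks are used.

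**Step 2: what a gap does to the planned contrast.** The group-by-time interaction compares within-person change between arms, so baseline is subtracted with coefficient 1. With correlation 0.5, the best prediction of later Berg uses coefficient 0.5. A gap of 0.4 SD therefore moves the expected change contrast by 0.4 × (1 − 0.5) = 0.2 SD, from 0.76 to 0.56 or 0.96 SD depending on direction.

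**Step 3: precision of the two analyses, 24 per arm.**
- Change score: SE = √(2(1 − 0.5) × 2/24) = 0.289 SD. Noncentrality is 0.76/0.289 = 2.63, and power on 46 df is 73%.
- Baseline as covariate: SE = √((1 − 0.5²) × 2/24) = 0.250 SD. Noncentrality is 0.76/0.250 = 3.04, and power on 45 df is 84%. Simulation with equal arms agreed, at 74% and 84%.

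The same formulas at other correlations, with a small allowance for estimating the covariate slope, give 59% against 76% at 0.3 and 91% against 95% at 0.7. The gain shrinks as the correlation rises.

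**Step 4: what stratification adds.** A cut at the median multiplies the variance of the baseline gap by 1 − 2/π = 0.363, so its SD is 0.289 × √0.363 = 0.174 SD. The chance of a gap above 0.3 SD falls to 8% (9% in simulation) and above 0.5 SD to about 0.4% (0.5%). If the cut puts only 20% of participants in one stratum, the variance factor is about 0.51 and the chance above 0.3 SD is about 15%. At 10% it is about 20%.

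Simulated power for simple, blocked and stratified-block allocation was 72%, 74% and 75% for change scores, and 83%, 84% and 84% with baseline adjusted for.

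**The case against.** **The sequence may not be unrestricted.** A reader might infer that 2.3 describes coin-toss allocation with arm sizes left to chance. The text does not say so: it is silent on blocks, and a condensed article may leave block sizes to the full protocol. The chances of a 28:20 split or worse (31%) and of 30:18 or worse (11%) hold only without blocks. Even then the loss is small: 4 × 28 × 20/48² = 0.972 and 4 × 30 × 18/48² = 0.9375, that is about 3% and 6% of the effective sample. The lack of Berg strata rests on firmer ground, because strata would need an envelope series each and only one is described.

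**Imbalance is not likely.** A reader might infer that the wide entry range makes a serious gap probable. It does not. In SD units the probability depends on the number of participants, and most trials of this size would have no gap above 0.3 SD. The range from 0 to 55 is a formal limit, not an expected spread; a wide spread only makes a given gap larger in points.

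**Chance imbalance is not bias.** This is correct. Over repeated randomisations the change contrast is unbiased, and its SE of 0.289 SD already includes baseline variation. The 0.2 SD shift in step 2 is less than one SE. What remains is that the SE is larger than it needs to be, and that an observed imbalance has no agreed handling.

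**The plan does provide for adjustment.** It does, but only conditionally, with no trigger and no named covariate. That does not secure the gain in step 3.

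**Stratified blocks have a price.** The researchers who request the envelopes are not blinded to the interventions. In two small strata with short blocks, some assignments could be guessed. This objection stands, and it is one reason why stratification is only the secondary suggestion.

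**Conclusion.** The point holds at modest weight. Baseline Berg is known before allocation, is not used to balance the arms, and enters the planned analysis only as one of the repeated outcomes unless imbalance is observed. The chance of a gap is about 30% above 0.3 SD and about 8% above 0.5 SD with 24 per arm.

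The weakness that matters most is in section 2.6. A fixed adjustment for baseline would raise power from about 73% to 84%, on data already being collected. This rests on reading 0.380 as Cohen's f, a correlation of 0.5, roughly normal scores, a single post-baseline comparison and 48 analysed participants. Stratified allocation would make the baseline table more reassuring but adds only about 1 point of power once the model is adjusted, or up to about 3 points if it is not. The documents do not support calling the allocation method faulty or the result biased.

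**What to change.** **Main change, section 2.6.** State that the primary analysis models post-baseline Berg (ANCOVA, or a mixed model for T1 and T2) with treatment group and with baseline Berg as a prespecified covariate, whatever imbalance is observed. Delete subgroup analysis as the response to baseline differences, and replace the conditional adjustment sentence with this fixed one. The cost is a few sentences; no extra data or visits are needed.

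**Optional, section 2.3, before the first envelope is opened.** State whether blocks are used. If stratification is wanted, use two strata from one baseline Berg cut fixed in advance and expected to lie near the median. Use permuted blocks of randomly varying size, concealed from the enrolling researchers, and avoid blocks of 2. Keep the stratum or baseline Berg in the model. The cost is a new list, a second envelope series, one extra check by the secretary, possibly an incomplete block per stratum, and some residual predictability. The benefit shrinks if the cut falls far from the median.
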